### Statistical analysis

#### Objective 1: descriptive analysis

We will derive point prevalence of neurodisability at the start of Year 7 (defined as the number of pupils with a hospital or school record of neurodisability at any point before they entered Year 7 divided by the number of pupils enrolled in Year 7), overall and by neurodisability subgroup. Children with neurodisability are more likely to live in more socioeconomically disadvantaged households, experiencing multiple social determinants of health which may affect their underlying health needs as well as their access to support services. We will describe numbers and percentages for adolescents according to baseline sociodemographic characteristics (table 2) to understand potential overlaps in factors contributing to health inequalities. NPD and HES are likely to capture adolescents with different levels of health need, we will therefore also describe the overlap and baseline characteristics of adolescents with neurodisability captured in education and health datasets. We will also compare mortality rates in adolescents with neurodisability, overall and according to data source used as a crude measure of complexity of health needs.

ECHILD does not capture termly data on children and young people educated in the private sector (approximately 7% of pupils in England each year).^34^ We will estimate the number of adolescents lost at the start of Year 7 due to being educated outside of state-funded schools. This is defined as the difference in the number of pupils ever enrolled in state-funded primary school and alive in Year 7 and the number of adolescents enrolled in Year 7.

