### Study population and follow-up

We will develop a cohort of secondary school aged adolescents enrolled in state-funded schools in Year 7 (usually aged 11–12 years old) between 2008/2009 and 2014/2015. We will exclude young people who are 2 or more years outside of their expected age for their school year.

Adolescents will be followed up from 1 February (after the spring school census) in Year 7 through to Year 11 (the end of secondary school, usually aged 15–16 years old) in education records, and until aged 22 in healthcare records (due to data availability) (figure 1). Education outcomes will be measured until the end of term 1 of the 2019/2020 academic year (31 December 2019) in education records, the last full academic term before the COVID-19 pandemic. Healthcare outcomes will be measured up until 1 March 2020, just before the first COVID-19 lockdown in England, as the pandemic impacted access to school and the frequency of hospital contacts captured in ECHILD data.^36 37^

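### The estimate of pupils lost to non-state schooling subtracts a Year 7 count not limited to former state primary pupils, and attributes every exit except death to non-state education

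*Protocol article*

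**What the plan says.** The protocol article, under *Objective 1: descriptive analysis*, states the target: "We will estimate the number of adolescents lost at the start of Year 7 due to being educated outside of state-funded schools". It then gives a formula. The first term is "the difference in the number of pupils ever enrolled in state-funded primary school and alive in Year 7"; the second, which is subtracted, is "the number of adolescents enrolled in Year 7". Nothing in that sentence limits the second term to pupils counted in the first.

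Under *Study population and follow-up*, entry to the cohort depends only on Year 7 enrolment: "We will develop a cohort of secondary school aged adolescents enrolled in state-funded schools in Year 7". Earlier attendance at a state primary school is not required. The same section adds an age restriction: "We will exclude young people who are 2 or more years outside of their expected age for their school year". The Objective 1 text does not say whether the Year 7 count is taken before or after that restriction.

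The only exit that the formula removes is death, through the words "alive in Year 7".

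**The concern.** The protocol names one cause of loss, education outside state-funded schools, but the formula measures something broader and possibly netted. There are two separate problems.

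- **Cancellation.** Pupils who enter a state-funded Year 7 from private primaries or from abroad are in the second count and not in the first. In a subtraction of headcounts, each one offsets a real loss.
- **Attribution.** A child who attended state primary at any time and then emigrated, moved to another part of the UK or could not be linked is in the first count and not in the second. Each is counted as a loss to non-state schooling.

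At stake is how the cohort's coverage at entry is described. Entrants also matter in their own right. The school-based route to identifying neurodisability uses special educational needs records from Years 1–6. Pupils with no state primary record cannot be found by that route, and recent arrivals from abroad may have little hospital history in England. A net figure hides this group.

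**Working it through.** The protocol states no count or rate for this estimate, so there is no figure to reproduce. The check is an accounting identity.

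**Definitions**

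- P: pupils ever in state-funded primary and alive in Year 7 (first term, Objective 1).
- Y: adolescents enrolled in state-funded Year 7 (second term, Objective 1; entry rule in *Study population and follow-up*).
- N: members of P educated outside state-funded schools at Year 7. This is the stated target. Home-educated pupils belong here.
- O: members of P absent from state-funded Year 7 for any other reason.
- E: members of Y who were never in state-funded primary.

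**Identity**

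Y = P − N − O + E, so

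- headcount difference: P − Y = N + O − E
- pupil-level set difference (in P, not in Y): N + O

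The headcount difference misses the target by O − E. It is right only if O = E, and is negative only if E > N + O. The set difference exceeds the target by O and cannot be negative.

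**Illustration.** All flows are assumptions, per 100,000 pupils in P.

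| N (target) | O | E | Headcount N + O − E | Set difference N + O |
|---|---|---|---|---|
| 4,000 | 1,000 | 1,000 | 4,000 | 5,000 |
| 4,000 | 1,000 | 3,000 | 2,000 | 5,000 |
| 4,000 | 3,000 | 0 | 7,000 | 7,000 |
| 4,000 | 1,000 | 6,000 | −1,000 | 5,000 |

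Letting N run over 2–7%, O over 0–3% and E over 0–6%:

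- target: 2,000 to 7,000
- headcount difference: from 2,000 + 0 − 6,000 = −4,000 to 7,000 + 3,000 − 0 = 10,000
- set difference: from 2,000 + 0 = 2,000 to 7,000 + 3,000 = 10,000, exceeding the target by 0 to 3,000

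These ranges show how the formula behaves. They are not predictions for this cohort.

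**The case against.** The strongest reply is that the data are linked at pupil level and the authors probably mean a nested comparison: of the pupils once in state primary and still alive, how many appear in Year 7. Only a pupil already in the primary group can be lost from it, and checking vital status already implies following individuals. A condensed article may leave the matching step to code. This is fair, and on that reading the cancellation disappears. The attribution problem does not, because death is still the only exit removed.

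Some stronger readings are tempting but the document does not support them.

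- **That the figure will be too small, or negative.** A negative value needs entrants to outnumber all exits together. Because the first term accumulates leavers over all primary years, an overestimate is equally possible.
- **That this is the only assessment of selection into the cohort, or that a small value would be read as negligible selection.** The article refers to a supplemental appendix on sources of bias, which is not shown. It openly lists state-school coverage as a limitation and nowhere says how a small value would be interpreted.
- **That the result can be judged against the private-sector share of "approximately 7% of pupils in England each year".** That share includes children who were never in state primary, and they are in neither term.
- **That pupils removed for age are counted as non-state losses.** This depends on when the Year 7 count is taken, which the text does not say.

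**Conclusion.** The point holds in limited form. The stated formula does not measure the stated target. As a headcount difference it is biased by other exits minus new entrants, with unknown sign and size. As a pupil-level difference it is too large by the number of other exits. In the assumed scenarios that excess is 0 to 3,000 per 100,000, while the headcount error (O − E) runs from −6,000 to 3,000. These sizes rest wholly on assumed flows.

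The consequence is modest. The figure describes coverage at cohort entry. It does not enter the prevalence estimate, the admission rates or the educational outcomes. It is worth correcting because the rule is explicit and the remedy is simple.

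**What to change.** - Define the figure as a pupil-level set difference: pupils with any state-funded primary record, alive at the start of Year 7, who have no state-funded Year 7 record.
- Keep the ever-enrolled base, since a Year 6 base alone would drop pupils who moved to private or home education earlier. The same figure for pupils on roll in Year 6 could be added.
- Report separately the Year 7 entrants with no state primary record.
- State whether the Year 7 count is taken before the age exclusion.
- Label the result *not observed in state-funded Year 7 for any reason*, and do not attribute it to non-state schooling.

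The cost is an anti-join on the pupil identifier in place of a subtraction, and a revised sentence or two. No new data are needed.

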#### Objective 2a: trends in planned and unplanned admissions

We will estimate rates of planned and unplanned healthcare contacts by age for adolescents with neurodisability (overall and by subgroup) and their peers. We will use Poisson or negative binomial regression models to estimate rate ratios for healthcare contacts for adolescents with neurodisability versus peers. We will assess whether trends in provision of planned support and unplanned healthcare contacts change before, during and after transition to adult healthcare (at ages 11–15, 16–18 and 19–22 years old, respectively) by including three binary indicators (intercepts) and three linear splines (slopes) for each age category (unless different specification is more appropriate on visual examination of figures). The intercepts indicate healthcare contact rates at baseline (11, 16 and 19 years old), while the slopes describe the rate of change as age increases. Models will include academic year of birth (to account for possible cohort effects) and we will also account for repeated measurements within pupils over time (eg, by allowing for a random effect by individual). We will test whether trajectories of healthcare use differ between adolescents with neurodisability and their peers by adding interaction terms between neurodisability and age variables.

We will also examine differences in support and outcomes among adolescents with neurodisability according to sociodemographic characteristics and school placement type (mainstream/special) at the start of Year 7. We will calculate and plot rates of planned and unplanned healthcare contacts by pupil characteristics, socioeconomic factors and school type for adolescents with and without neurodisability.

#### Objective 2b: trends in educational support, school attendance and exclusions

We will calculate and plot the proportion of pupils experiencing each educational outcome (defined as the number of pupils with at least one recording of the outcome divided by the number of pupils on school roll at the start of the given school year) by year of age. We will use a Poisson or logistic regression model to quantify the differences between adolescents with neurodisability and their peers. The models will include age, birth year and an indicator of neurodisability, and we will account for repeated measures per child. We will also graphically quantify changes in proportions of adolescents experiencing each outcome according to neurodisability subgroup and sociodemographic characteristics (separately for adolescents with neurodisability and their peers).

Analyses carried out for objectives 2a and 2b will reveal whether support and adverse outcomes across health and education follow similar trajectories with age for adolescents with neurodisability and their peers and illustrate potential inequalities in support and adverse outcomes to inform design of further studies.

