#### Outcome: educational outcomes

We will describe changes in educational support (measured as school-recorded SEN provision) and school participation (measured by absences and exclusions from school) per year of age across secondary school (between start of Year 7 and end of Year 11, or until loss of follow-up, death or 31 December 2019, whichever occurred first) for adolescents with neurodisability and unaffected peers. Our primary focus will be on persistent absences. Secondary outcomes will be medical/non-medical absences and exclusions. All outcomes are defined in table 1.

**Table 1 T1:** Definitions of educational outcomes

Outcomes		Definition	Dataset(s)	Measured
**School participation**	Persistent absentees	Pupils who miss 10% or more of their possible sessions^45^	NPD School Census	Year 7–Year 11 (11/12–15/16 years old)
	Absence for medical reasons	Authorised/unauthorised absences for doctor/dentist appointments or illness*		
	Absences for non-medical reasons	Authorised/unauthorised absences for all other reasons than medical*		
	Exclusions	Pupils with at least one suspension (fixed-period exclusion) or permanent exclusion in the given school year		
**Educational support**	SEN provision (by type)	SEN provision will be grouped in the following descending hierarchy: No SEN provision SEN support in mainstream school EHCP in mainstream school Enrolment in specialist provision		

* We will use the total number of possible sessions rather than pupils as denominator.

EHCP, Education, Health and Care PlanNPD, National Pupil Database; SEN, special educational needs

NPD data include some information about post-16 educational outcomes (such as special school attendance until 19 years old or education, employment or training at 17–18 years from National Client Caseload Information System),^34^ and we will explore the feasibility of using these data to examine educational trajectories of adolescents with neurodisability after secondary school.

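### Objective 2b applies a pupil-level any-recording proportion to all education outcomes, which contradicts the session denominator that Table 1 sets for medical and non-medical absence

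*Protocol article*

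**What the plan says.** The section on educational outcomes refers to Table 1 for all definitions. It makes persistent absence the primary education outcome ("Our primary focus will be on persistent absences") and medical absence, non-medical absence and exclusions secondary.

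In Table 1, two of the school participation outcomes are properties of a pupil. Persistent absence is "Pupils who miss 10% or more of their possible sessions", and exclusions are "Pupils with at least one suspension (fixed-period exclusion) or permanent exclusion in the given school year". SEN provision is a category assigned to each pupil.

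The other two describe absences and carry an asterisk: "Authorised/unauthorised absences for doctor/dentist appointments or illness" and "Authorised/unauthorised absences for all other reasons than medical". Neither has a threshold. The asterisk leads to the footnote "We will use the total number of possible sessions rather than pupils as denominator".

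The Objective 2b analysis section then announces a single kind of measure: "We will calculate and plot the proportion of pupils experiencing each educational outcome". The section spells out how that share is formed, namely "defined as the number of pupils with at least one recording of the outcome divided by the number of pupils on school roll", with the roll counted when each school year begins and results shown by year of age. It exempts no outcome. The plots by subgroup and sociodemographic characteristics are also described as proportions of adolescents for each outcome. The comparison of groups is to use Poisson or logistic regression, without saying which outcome gets which.

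**The concern.** For medical and non-medical absence the definitions table and the analysis section prescribe different quantities. One is the share of possible sessions that are missed. The other is the share of pupils with any such absence in the year. An analyst who codes from Objective 2b produces the second, and one who codes from Table 1 produces the first.

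The choice matters because the article wants to know how far adverse school outcomes differ between adolescents with neurodisability and their peers, and how this changes with age. Without a threshold, a single dental appointment and months of illness both count as one recording. Two groups can differ widely in time lost from school and still have similar proportions with any absence. Two groups or ages compared on the any-absence scale are therefore not compared on the quantity that Table 1 defines.

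**Working it through.** **Step 1: the two rules side by side.**

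| Outcome | Unit in Table 1 | Unit in Objective 2b | Agree? |
|---|---|---|---|
| Persistent absence (primary) | pupil, 10% threshold | pupil | yes |
| Exclusions (secondary) | pupil, at least one in the year | pupil | yes |
| SEN provision | pupil, category | pupil | yes |
| Medical absence (secondary) | sessions | pupil with at least one | no |
| Non-medical absence (secondary) | sessions | pupil with at least one | no |

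The conflict is confined to the last two rows.

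**Step 2: how far the two quantities can differ.** The documents give no absence rate, number of sessions or spell length, so there is no figure to reproduce. Every input below is an assumption made for illustration.

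*Equal risk for all pupils within a group.* With a mean of m absence spells a year following a Poisson distribution, P(any) = 1 − exp(−m).

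- m = 6 (neurodisability) v 4 (peers), rate ratio 1.5: 0.9975 / 0.9817 = 1.02.
- m = 3 v 2, rate ratio 1.5: 0.9502 / 0.8647 = 1.10.

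*Risk that varies between pupils.* Take S = 380 possible sessions a year, session absence rate r, mean spell length L sessions and gamma shape k. Then m = S·r/L and P(any) = 1 − (k/(k + m))^k. For example, with r = 3% v 5%, L = 2 and k = 1, m = 5.7 v 9.5, and P = 5.7/6.7 = 0.851 v 9.5/10.5 = 0.905.

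| Rates, peers v neurodisability | Session ratio | L, k | P(any), peers v neurodisability | Risk ratio |
|---|---|---|---|---|
| 3% v 5% | 1.67 | 2, 1 | 0.851 v 0.905 | 1.06 |
| 3% v 5% | 1.67 | 2, 2 | 0.933 v 0.970 | 1.04 |
| 3% v 5% | 1.67 | 4, 0.5 | 0.614 v 0.691 | 1.13 |
| 2% v 4% | 2.0 | 2, 2 | 0.881 v 0.957 | 1.09 |
| 1% v 2% | 2.0 | 2, 2 | 0.737 v 0.881 | 1.20 |
| 1% v 2% | 2.0 | 4, 1 | 0.487 v 0.655 | 1.35 |

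The any-absence risk ratio is closer to 1 than the session or spell ratio in every scenario run. It ranges from about 1.02 to 1.35 where the rate ratio is 1.5 to 2.0.

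**Step 3: the odds ratio.** Logistic regression is one of the two named models, so the odds scale has to be checked too. In the equal-risk case the odds of any absence are e^m − 1.

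- m = 6 v 4: (e^6 − 1)/(e^4 − 1) = 402.4/53.6 = 7.5.
- m = 3 v 2: (e^3 − 1)/(e^2 − 1) = 19.1/6.39 = 3.0.

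Both stand against a rate ratio of 1.5. When risk varies between pupils the answer depends on k. With k = 1 the odds equal m, so the odds ratio matches the session ratio exactly. For 3% v 5% (session ratio 1.67), k = 2 and L = 2 give (0.9698/0.0302)/(0.9325/0.0675) = 2.3, and k = 0.5 and L = 4 give (0.6914/0.3086)/(0.6137/0.3863) = 1.4. The odds ratio can therefore lie above, on or below the session ratio, depending on a feature of the data that is not known in advance.

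**Step 4: is any absence nearly universal?** Over r = 0.5% to 5% and S = 300 to 380, independent sessions give P(any) from 78% to nearly 100%. With spells and varying risk (L = 2 to 4, k = 0.5 to 2) the range is 24% to 97%. Near-universality follows only if absences are frequent or close to independent.

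**The case against.** The strongest reply is that the article settles the matter itself. Table 1 is named as the place where outcomes are defined, its footnote is specific, and its contrast with pupils reads as an exception to a pupil-based rule. A specific definition normally governs a general summary sentence. That is a fair reading, and it shows which rule was probably intended. It does not remove the conflict, because the analysis section covers each outcome without exception and uses proportions again for the subgroup plots.

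A second reply is that Poisson regression is named and could carry missed sessions with a session offset, a detail that a condensed article may leave out. This stands. The absence of an offset is not a fault in itself, and a reader should not infer that the session rate will never be modelled.

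Two further inferences are tempting and not supported. One is that the any-absence measure will be near 100% in both groups and so uninformative. The documents give no rates, and Step 4 shows a wide range, with less certainty for non-medical than for medical absence. The other is that the contrast must shrink towards no difference. That holds for the risk ratios in the scenarios run, but not for the odds ratio.

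**Conclusion.** The contradiction is real and can be read directly from the text. It affects two secondary education outcomes. The primary one, persistent absence, is untouched, as are exclusions and SEN provision.

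If the Objective 2b rule were followed, the analysis would discard the amount of absence and would not estimate the session-rate contrast that Table 1 implies. The size is illustrative only, about 1.02 to 1.35 as a risk ratio against a rate ratio of 1.5 to 2.0, and it rests wholly on assumed absence rates, spell lengths and variation between pupils. The odds ratio is not a reliable route back, since it matches the session ratio only in a special case.

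This is a conflict between two stated rules that should be resolved before analysis. It is not evidence that the education analysis as a whole is badly chosen.

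**What to change.** In Objective 2b, restrict the proportion of pupils on roll to persistent absence, exclusions and SEN provision. For medical and non-medical absence, state that sessions missed divided by possible sessions will be plotted by year of age and group, and use the same measure in the subgroup and sociodemographic plots. For the comparison of groups, model missed sessions as a count with log(possible sessions) as offset, allowing for overdispersion and for the repeated measures per child that are already planned.

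The cost is one or two sentences and a different model call for two outcomes. Table 1 already commits to possible sessions as the denominator, so no new data item is needed.

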**Methods and analysis:**

Using the Education and Child Health Insights from Linked Data (ECHILD) database, which links health and education data across England, we will follow adolescents from the start of secondary school (Year 7) into early adulthood. We will classify children with and without neurodisability recorded in hospital and education records before Year 7, compare their sociodemographic characteristics and describe trends in health and educational outcomes throughout secondary school. We will estimate rates of planned and unplanned healthcare contacts by year of age (11–22 years old), and we will examine changes in trends before, during and after transition to adult healthcare. We will also estimate the proportion of adolescents with school-recorded SEN provision and rates of school absences and exclusions by year of age (11–15 years old) for the two groups. We will explore variation in outcomes by neurodisability subgroup and sociodemographic characteristics and contextualise the findings using existing interview and survey data from children, young people and parents/carers generated in the Health Outcomes of young People throughout Education (HOPE) research programme.

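### The objective 2b regression has no neurodisability-by-age term, so it cannot estimate or test whether education trajectories differ, although the 2a and 2b analyses are said to reveal this

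*Protocol article*

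**What the plan says.** Under Statistical analysis, Objective 2b, three things are planned.

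- Description: "We will calculate and plot the proportion of pupils experiencing each educational outcome", by year of age. The abstract's Methods and analysis paragraph promises the same for ages 11 to 15 in the two groups: "We will also estimate the proportion of adolescents with school-recorded SEN provision and rates of school absences and exclusions by year of age".
- Regression: "We will use a Poisson or logistic regression model to quantify the differences between adolescents with neurodisability and their peers". The terms are then listed: "The models will include age, birth year and an indicator of neurodisability, and we will account for repeated measures per child".
- Graphs by neurodisability subgroup and sociodemographic characteristics, drawn "separately for adolescents with neurodisability and their peers".

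The section closes with a claim made jointly for 2a and 2b, namely that these analyses "will reveal whether support and adverse outcomes across health and education follow similar trajectories with age for adolescents with neurodisability and their peers".

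Objective 2a, immediately before, sets out to test whether healthcare trajectories differ between the groups, and does so "by adding interaction terms between neurodisability and age variables".

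**The concern.** Two parallel objectives feed one shared conclusion about trajectories, but only the healthcare model has the term that lets trajectories differ between groups. The 2b term list has a neurodisability indicator and age, with nothing linking them. How support and school participation change with age in the two groups is the education half of the study's aim. Persistent absence, the primary education focus, is affected along with the other 2b outcomes.

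If the model is run as listed, the paper would report one ratio per outcome. A reader could take it as applying equally in Year 7 and Year 11, when the model has assumed that rather than found it.

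**Working it through.** **No figure to reproduce.** The article gives no sample size, effect size or outcome proportion for 2b. The structural result in step 1 needs no data. Steps 2 and 3 use assumed proportions and only illustrate possible size.

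**Step 1: what the listed terms imply.** Let p be the probability of the outcome, g the log or logit link, and ND the neurodisability indicator (1 or 0):

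g(p) = a + f(age) + h(birth year) + b × ND

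At any age and birth year, g(p | ND=1) − g(p | ND=0) = b. The ratio (log link) or odds ratio (logit link) is exp(b) at every age, whatever form f takes. Accounting for repeated measures adds no parameter that lets b vary with age; with a pupil-level random effect, the constant ratio is the one conditional on the pupil. With an interaction the contrast becomes b + c(age), and testing c = 0 is the test of similar trajectories on that scale.

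**Step 2: what the single ratio would be.** With age as five categories, a log link and the same ratio of group sizes at each age, the Poisson estimate reduces to

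exp(b) = (sum of the five ND proportions) / (sum of the five peer proportions).

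**Step 3: four assumed patterns over the five years.** Birth year is left out for simplicity. Group sizes per age are assumed at 60,000 ND and 500,000 peers in A, and 10,000 and 90,000 in B to D.

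| Pattern | ND, % | Peers, % | True risk ratio, first to last year | Single risk ratio from the listed model |
|---|---|---|---|---|
| A, ratio falling | 16, 19, 22, 25, 28 | 6, 8.5, 11, 13.5, 16 | 2.67, 2.24, 2.00, 1.85, 1.75 | 110/55 = 2.00 |
| B, ratio rising | 14, 18, 22, 26, 30 | 10, 11, 12, 13, 14 | 1.40, 1.64, 1.83, 2.00, 2.14 | 110/60 = 1.83 |
| C, mild | 16, 18, 20, 22, 24 | 10, 11, 12, 13, 14 | 1.60, 1.64, 1.67, 1.69, 1.71 | 100/60 = 1.67 |
| D, crossing | 8, 10, 12, 14.5, 17 | 10, 11, 12, 13, 14 | 0.80, 0.91, 1.00, 1.12, 1.21 | 61.5/60 = 1.025 |

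Error of the single risk ratio in the first and last year:

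- A: 2.00/2.667 = 0.75 (25% too low); 2.00/1.75 = 1.14 (14% too high).
- B: 1.833/1.40 = 1.31 (31% too high); 1.833/2.143 = 0.86 (14% too low).
- C: 1.667/1.60 = 1.04 (4% too high); 1.667/1.714 = 0.97 (3% too low).
- D: 1.025/0.80 = 1.28 (28% too high); 1.025/1.214 = 0.84 (16% too low). A change from lower to higher risk is reported as almost no difference.

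The logistic version behaves the same way. Its single odds ratio, against the true first-to-last values, is 2.31 (2.98 to 2.04) in A, 2.07 (1.47 to 2.63) in B, 1.84 (1.71 to 1.94) in C and 1.03 (0.78 to 1.26) in D.

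**Step 4: scale.** The constraint is on the ratio or odds scale. Absolute differences can still vary with age, but only as the constant ratio dictates. In B the true gap widens from 4 to 16 percentage points, while the logistic main-effects fit gives 8.4 to 11.5. In A the true ratio falls while the true gap rises from 10 to 12 points, so what counts as similar depends on the scale chosen.

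**The case against.** The strongest reply is that the regression is not the whole of 2b. Proportions by year of age are planned for both groups and impose no parallelism. The closing sentence credits the trajectory comparison to the analyses of 2a and 2b, not to the 2b model, whose stated job is only to quantify group differences. The study calls itself descriptive, and the article uses the language of testing for healthcare but not for education.

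Much of this stands. A reader might infer that objective 2b cannot show whether education trajectories differ at all. The article does not support that: the age-specific proportions can show divergence, and ratios follow from them by arithmetic. Nor is cohort imbalance in those plots an obvious danger. The last entry cohort (2014/2015) would, on normal progression, be in Year 11 in 2018/2019, before the 31 December 2019 cut-off. What the plots lack is a stated birth-year-adjusted contrast, an interval and a test.

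A second reply is that this is a condensed article and an unseen analysis plan may add the interaction. That is possible. But the 2b terms are listed, and the preceding section names the interaction for the same kind of question, so the stated text is mismatched with its stated purpose. Being descriptive does not explain the difference either, since 2a is equally descriptive.

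A third reply is that the distortion may be trivial. Pattern C shows that it may be.

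**Conclusion.** The point holds for the 2b regression. As listed, it fixes one neurodisability-versus-peer ratio at all ages on the log or logit scale and has no parameter that can estimate or test a difference in trajectory. That follows from the term list alone. The size of the consequence is unknown: the largest error in the risk ratio is 4% in the mildest assumed pattern and 25% to 31% in the other three, one of which hides a reversal. None of these patterns is study data.

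This should be fixed before analysis, but it does not undermine the objective, because unmodelled age-specific proportions are already planned for both groups.

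**What to change.** Add neurodisability-by-age terms to the 2b models, as in 2a. Age as categories is a natural choice with only five school years, though other forms would serve. Report age-specific ratios and differences in proportions with intervals for each outcome, and the interaction test if one is wanted in parallel with 2a. With age in five categories the cost is four extra coefficients per model and a longer results table; in a national cohort the loss of precision should be small.

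If the authors prefer to keep the model as listed, they should state that education trajectories are compared only descriptively, through the proportions by year of age, and that the model ratio is an average over ages. That costs two sentences.
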